### Data collection and management

2.8

Data will be processed anonymously, omitting the information that can identify the participant's individual identity. Strict safety and confidentiality measures will be established in the archives of clinical trial institutions.

### Sample size calculation

2.9

We calculated the number of patients needed considering the epidemiology of MSI in RC and previous report by Wu et al.^[21]^ Test for 1 receiver operating characteristic (ROC) curve analysis showed that a sample of 33 from the MSI group and 297 from the MSS group could achieve 95% power to detect a difference of the null hypothesis (area under the curve [AUC] = 0.70) and the alternative hypothesis (AUC = 0.85), which was calculated by PASS 2019 (NCSS Statistical Software).

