**Method::**

All patients with RC were retrospectively enrolled. The dataset was randomly split into training cohort (70% of all patients) and testing cohort (30% of all patients). The radiomics features will be extracted from T2WI–MR images of the entire primary tumor region. Least absolute shrinkage and selection operator was used to select the most predictive radiomics features. Logistic regression models were constructed in the training/validation cohort to discriminate the MSI status using clinical factors, radiomics features, or their integration. The diagnostic performance of these 3 models was evaluated in the testing cohort based on their area under the curve, sensitivity, specificity, and accuracy.

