### Outcome measure

2.7

The radiomics model which identify potential differences between RC without MSI-H group and RC with MSI-H group will be the outcome measure.

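### The stated 95% power applies to 33 MSI and 297 MSS patients, but the AUC is evaluated in a 30% testing cohort (about 10 and 89), where the same formula gives about 40%

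*Protocol article*

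**What the plan says.** Section 2.9 (Sample size calculation) introduces its figures as a count of patients: "We calculated the number of patients needed considering the epidemiology of MSI in RC". The method is a "Test for 1 receiver operating characteristic (ROC) curve analysis", with "null hypothesis (area under the curve [AUC] = 0.70" and "alternative hypothesis (AUC = 0.85" as the two values. The result is that "a sample of 33 from the MSI group and 297 from the MSS group could achieve 95% power". The section states no alpha and does not mention any division of the data.

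The division is in the Method paragraph of the abstract: "The dataset was randomly split into training cohort (70% of all patients) and testing cohort (30% of all patients". The same paragraph says where the AUC is assessed: "The diagnostic performance of these 3 models was evaluated in the testing cohort".

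Sections 2.6.5 and 2.6.6 show what the other patients are for. Low-variance features are removed using the training data, and five-fold cross-validation is run within the training/validation cohort to build the models. Section 2.10 asks for an AUC for each model without naming a cohort, and sets a general two-sided 0.05 significance level.

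**The concern.** The power of a test of one AUC depends on the patients in whom that AUC is estimated, above all on the number in the smaller group. If 33 MSI patients are the whole supply and 30% go to the testing cohort, only about 10 inform the reported AUC. The other 70% select features and fit the models. Their AUC is optimistic and cannot count as independent test data.

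A reader told that the design has 95% power would take a testing-cohort result that fails to exclude 0.70 as strong evidence against the T2WI hypothesis. With about 10 MSI patients, such a result would be quite likely even if the true AUC were 0.85. Sensitivity, another of the stated measures, rests on the same 10 or so patients.

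**Working it through.** **Inputs.** Section 2.9: 33 MSI, 297 MSS, null AUC 0.70, alternative AUC 0.85, stated power 95%. Abstract, Method: 30% testing share. Section 2.10: two-sided 0.05, borrowed here because 2.9 gives no alpha.

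**Testing cohort.** 0.30 × 33 = 9.9 MSI and 0.30 × 297 = 89.1 MSS, so about 10 and 89.

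**Formula.** Power = Φ((0.85 − 0.70 − 1.96·SE0)/SE1), where SE0 and SE1 are the standard errors of the AUC under the null and the alternative. For binormal continuous scores with equal standard deviations, with n1 MSI patients and R = MSS/MSI:

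- a = √2·Φ⁻¹(AUC), f = exp(−a²/4)/√(4π), g = −a·f/2
- SE² = [f²(1 + 1/R + a²/2) + g²(1 + R)/(2R) + a·f·g]/n1

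With R = 9, the bracket is 0.0718 at AUC 0.70 (a = 0.742, f = 0.2459, g = −0.0912) and 0.0383 at AUC 0.85 (a = 1.466, f = 0.1649, g = −0.1208).

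**Reproducing the stated figure, 33/297.** SE0 = √(0.0718/33) = 0.0466 and SE1 = √(0.0383/33) = 0.0341. Power = Φ((0.15 − 1.96 × 0.0466)/0.0341) = Φ(1.72) = 95.7%. The stated 95% is sound for these numbers.

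**Testing cohort, 10/89.** R = 8.9, SE0 = 0.0848, SE1 = 0.0619. Power = Φ((0.15 − 1.96 × 0.0848)/0.0619) = Φ(−0.26) = 39.7%. Put another way, the observed AUC would have to exceed 0.70 + 1.96 × 0.0848 = 0.866, which is above the true value assumed.

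**Other choices**

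| Method | 33/297 | 10/89 |
|---|---|---|
| Binormal, two-sided 0.05 | 95.7% | 39.7% |
| Hanley-McNeil, two-sided 0.05 | 86.1% | 31.0% |
| Obuchowski approximation, two-sided 0.05 | 86.0% | 34.0% |
| The same three formulas, one-sided 0.05 | 92.5–98.4% | 45.7–56.8% |
| The same three, two-sided, alternative variance only | 91.4–99.3% | 44.8–67.8% |
| Simulated Hanley-McNeil test with null SE | 90.4% | 29.3% |
| Simulated DeLong test, logit scale | 93.7% | 47.4% |
| Simulated DeLong test, Wald | 96.2% | 63.7% |

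The DeLong Wald test at 10/89 has an upper-tail false-positive rate of 7.0% against a nominal 2.5%, so part of its power is not real. Relaxing both choices at once (binormal, one-sided, alternative variance only) gives 78.1% at 10/89, but that combination gives 99.7% at 33/297 and so does not match the stated 95%.

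**Precision.** Around an AUC of 0.85, the 95% half-width is 1.96 × 0.0341 = 0.07 at 33/297 and 1.96 × 0.0619 = 0.12 at 10/89.

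**Random split.** If the split is not stratified by MSI status, the number of MSI patients tested has mean 9.9 and SD 2.5, with a 95% range of 5 to 15. The binormal power is 35.5% at 9/90 and 43.8% at 11/88.

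**Total needed for 95% in the testing cohort.** The binormal formula reaches 95% at 32/288, so 320/0.30 ≈ 1,070 patients. Taking 33/297 itself gives 330/0.30 = 1,100.

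**The case against.** The strongest reply is that section 2.9 never says 33 and 297 make up the whole dataset. No total enrolment is given, the 70/30 split appears only in the abstract, and section 2.10 names no cohort for the AUC. The figures could have been meant for the testing cohort. That reading cannot be excluded, but the text does not support it: the section introduces its figures as the patients needed, and the roughly 1,070 to 1,100 patients that this reading requires appear nowhere.

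A second reply is that section 2.9 fixes neither alpha nor the form of the test. This stands, and it limits what can be claimed. A reader might infer that power is firmly 30–40%, or that a model with a true AUC of 0.85 would more likely than not fail. Both hold for the standard two-sided formulas with null and alternative variances, but not for every test the authors might use, as the DeLong Wald figure of 64% shows. Nor does reproducing 95% identify the software setting: a one-sided Obuchowski calculation with alternative variance only gives 95.3% at 33/297 and 57.3% at 10/89. None of this brings power near 95%.

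A third reply is that a condensed article leaves detail elsewhere. That would answer an omission, but here the sample size, the split and the evaluation cohort are all stated, and they do not fit together.

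**Conclusion.** The power statement is wrong as written for the evaluation described. The 95% figure is not a calculation error, since it reproduces at 33/297. The fault is that it is attached to a cohort in which the AUC is not evaluated. In a testing cohort of about 10 MSI and 89 MSS, power is about 40% by the binormal formula that reproduces the stated figure, and about 30% to 68% when formula or test is varied one choice at a time.

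This rests on three assumptions: 33/297 is the full dataset, alpha is the two-sided 0.05 of section 2.10, and the testing cohort has roughly the same MSI proportion as the whole.

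A reader might go further and fault sections 2.7 and 2.10 for not repeating the test against 0.70. In a condensed article without its analysis plan, that detail may lie elsewhere, and the power mismatch does not depend on it.

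**What to change.** In section 2.9, restate the power and the expected confidence interval for the testing cohort actually evaluated: about 40% power and a 95% half-width of about 0.12 with 10 MSI and 89 MSS, naming the alpha, sidedness and test assumed. If 33/297 was meant as the testing cohort, say so and state the implied total of about 1,070 to 1,100 patients.

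The cost is a few sentences and a much less favourable stated power. The restatement needs no new patients.

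An optional alternative is resampling-based validation on all patients, with feature selection and model fitting repeated inside each fold, so that every MSI patient contributes to the estimate. It should not be presented as restoring 95%. The out-of-fold predictions come from different fitted models and are correlated, so the one-curve variance does not apply directly, and no power has been shown for it.

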### Statistical analysis

2.10

The ROC curve analysis was conducted, and AUC, accuracy, sensitivity, and specificity were calculated to evaluate the diagnostic performance of each model. Mann–Whitney *U* test and Chi-squared test or Fisher exact test were performed to evaluate the differences in variables with a continuous distribution across categories and the association among categorical variables, respectively. A 2-sided *P*-value of <.05 was considered as statistically significant. Prism 5 for Windows (Version 5.01) and MedCalc (Version 18.11.3) were used for statistical analysis.

### Ethics and dissemination

2.11

This retrospective study was approved by the Biomedical Research Ethics Committee of West China Hospital of Sichuan University (No. 2019-1159), and the requirement for informed consent was waived. To protect privacy of participants, all of private information were anonymous. The results will be published in a peer-reviewed journal and will be disseminated electronically and in print regardless of results. The authors report no conflicts of interest.

## Discussion

3

Radiomics, the high-throughput mining of quantitative image features from standard-of-care medical imaging that enables data to be extracted and applied within clinical-decision support systems to improve diagnostic, prognostic, and predictive accuracy, is gaining importance in cancer research. Radiomic analysis exploits sophisticated image analysis tools and the rapid development and validation of medical imaging data that uses image-based signatures for precision diagnosis and treatment, providing a powerful tool in modern medicine.^[22]^ In this study, we will develop a radiomics model based on T2WI images to preoperative identify MSI status of RC. The model may provide a preoperative, and easy-to-use tool for MSI status diagnosis, which can help oncologists make better treatment choices for RC patients.

Our study has several limitations. We used the retrospective datasets to develop radiomics model, of which some clinical factors were not initially available on account of incomplete data. The ROIs were delineated in 1 single slice (2D), which might not be representative of the entire tumor. As a single-center retrospective study, the model needs to be validated by future multicenter studies to evaluate or improve the performance.

We hope that the radiomics model can be an excellent prediction performance on MSI status of RC and may have significant clinical implications on noninvasive assessment of MSI status for RC.
